## Abstract

**Background:**

Thoracolumbar fractures are most frequent along the spine, and surgical treatment is indicated for unstable fractures. Percutaneous minimally invasive surgery was introduced to reduce the pain associated with the open posterior approach and reduce the morbidity of the procedure by avoiding damage and dissection of the paravertebral muscles. The goal of this study is to compare the surgical treatment of fractures of the thoracolumbar spine treated by the conventional open approach and the percutaneous minimally invasive approach using similar types of pedicle spine fixation systems.

**Methods/designs:**

This study is designed as a multi-center, randomized controlled trial of patients aged 18–65 years who are scheduled to undergo surgical posterior fixation. Treatment by the conventional open approach or percutaneous minimally invasive approach will be randomly assigned. The primary outcome measure is postoperative pain, which will be measured using the visual analogue scale (VAS). The secondary outcome parameters are intraoperative bleeding, postoperative drainage, surgery time, length of hospital stay, SF-36, EQ-5D-5 l, HADS, pain medication, deambulation after surgery, intraoperative fluoroscopy time, vertebral segment kyphosis, fracture vertebral body height, compression of the vertebral canal, accuracy of the pedicle screws, and breakage or release of the implants. Patient will be followed up for 1, 2, 3, 6, 12 and 24 months postoperatively and evaluated according to the outcomes using clinical and radiological examinations, plain radiographs and computed tomografy (CT).

**Discussion:**

Surgical treatment of thoracolumbar fractures by the open or percutaneous minimally invasive approach will be compared in a multicenter randomized study using similar types of fixation systems, and the results will be evaluated according to clinical and radiological parameters at 1, 2, 3, 6, 12 and 24 months of follow-up.

**Trial registration:**

ClinicalTrial.gov approval number: 1.933.631, code: NCT03316703 in may 2017.

## Background

Thoracolumbar spine fractures are the most frequent fractures of the axial skeleton, and approximately two-thirds of these fractures occur between T11 and L2 [1]. Surgical treatment has been indicated for unstable fractures to stabilize the injured vertebral segment and allow early rehabilitation without ortheses or bed rest [2]. Conventional surgical treatment is performed by posterior fixation and arthrodesis of the injured vertebral segment using a pedicle fixation system with or without arthrodesis. This approach is performed via the open posterior approach over the midline [3–5].

Less invasive procedures are a growing trend in spinal surgery with an aim of minimizing tissue trauma, reducing blood loss and facilitating patient recovery. The use of percutaneous pedicle screws is part of minimally invasive procedures of the spine, and they can be applied in surgical procedures that use a fixation system mainly for treatment of fractures, degenerative diseases and tumors [6, 7].

The use of percutaneous pedicle screw fixation for the treatment of thoracolumbar fractures has been reported and is believed to have the advantages of the open approach (i.e., restoration of the alignment and stabilization of the vertebral segment) without its morbidity. Minimally invasive percutaneous pedicle screw fixation obtains results similar to those of traditional open surgery and has the advantages of less trauma, bleeding, and pain and rapid post-operative recovery [8, 9].

Recently, reports of the outcomes of surgical treatment of thoracolumbar spine fractures through the percutaneous pedicle spine have been increasing. However, randomized clinical trials are still rare, and more of these trials are needed to demonstrate the advantages of minimally invasive percutaneous pedicle screw fixation over the traditional open technique. The objective of the study is to compare the surgical treatment of fractures of the thoracolumbar spine using the conventional open approach or the minimally invasive percutaneous approach for stabilization of the affected vertebral segment with a similar type of pedicle spinal fixation system.

## Methods/design

This will be a multi-center randomized controlled trial to assess the effect of minimally invasive percutaneous surgery versus conventional open surgery in patients with thoracolumbar spine fractures with an indication for posterior stabilization. The primary endpoint will be the postoperative pain, evaluated through the visual analogue scale (VAS) and compared between the patients subjected to minimally invasive percutaneous surgery and those subjected to conventional open surgery. The follow-up period will be two years, during which time the patients will fill out questionnaires and be evaluated both clinically and radiologically. Conventional open surgery and minimally invasive percutaneous surgery will be compared in patients with thoracolumbar spine fractures with indication for posterior stabilization. The study is designed as a multi-center (five centers) study. The follow-up period is 2 years, during which time the patients will fill out questionnaires and be evaluated both clinically and radiologically.

### Patient selection

Patients of both sexes aged 18–65 years with fractures of the thoracolumbar spine and an indication for posterior fixation (one-level fracture, regional kyphosis > 30 degrees, regional kyphosis with osseous or ligamentous lesion, collapsed vertebral body > 50%, three vertebral column lesion, or unstable lesion) will be enrolled.

The indication and options for surgical treatment will be presented to patients who meet the inclusion criteria (Table 1). The patient will be informed about the objectives, investigative design, assessment and possible advantages and disadvantages of the proposed treatment. The patient will be asked to sign the informed consent form. Pre-operative baseline data will be collected for the outcome scores, patient demographic characteristics and classification and characterization of the injured vertebral segment.

**Table 1 Tab1:** Selection criteria

Inclusion criteria	
One level fracture	
Fracture T11-L5	
Adult (18–65 years old)	
Indication for posterior fixation	
Exclusion criteria	
More than one level fracture	
Osteoporotic fracture	
Pathological fracture	
Previous spinal surgery	
Spinal deformity	
Mental illness	
TCE	
Indication for posterior canal decompression	

Neurological deficit is considered in the evaluation but not in the inclusion or exclusion criteria, unless there is an indication for posterior decompression. The patients with neurological deficit that do not need a posterior decompression can be enrolled in the study if there is an indication for posterior fixation. In patients with total neurological déficit and no indication for canal decompression the treatment can be performed just by a posterior approach. In patients with neurological deficit with indication for anterior decompression of the vertebral canal after posterior fixation can also be included in the study.

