### Randomization

Patients who meet the inclusion criteria and have provided informed consent will have their fractures classified according to the system proposed by Magerl et al. The randomization process will be performed for each fracture type (A, B and C). The patients will be randomly allocated into the following two groups: A- conventional open surgery and B- minimally invasive percutaneous surgery. The randomization will be performed via a centralized system. The research team will contact the central randomization system informing the type of fracture (A, B or C). The type of treatment will then be assigned by this system, with the patient being subsequently allocated to the appropriate group. We will use envelopes for each fracture type, following the CONSORT (Consolidated Standards of Reporting Trials) guidelines. The randomization will be performed using numbers generated by a specific software [MedCalc Statistical Software version 18.11.3] and will obey the 1:1 ratio for each group [MedCalc Software bvba, Ostend, Belgium; https://www.medcalc.org; 2019].”general anesthesia. Stability of the spine will be achieved by bilateral short-segment pedicle instrumentation. Pedicle screws will be inserted into the vertebral body one level above and below the fractured vertebra. The fractured vertebra will also be included in the fixation. In the fractured vertebra, a short pedicle screw will be inserted uni- or bilaterally according to the degree of pedicle involvement.

The spine fixation system is composed of a 6.5-mm-diameter polyaxial pedicle screw attached to 5.5 mm rods. The vertebral fixation system will be applied through the conventional open approach in group A (open approach) and percutaneously without open exposition of the injured vertebral segment in group B (minimally invasive percutaneous surgery). Posterior fusion using bone grafts or bone substitutes will not be performed in either group. External immobilization will not be used after surgery, and the patients will be allowed to walk according to their general clinical picture and pain.

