### Outcome measurements

At admission, demographic, clinical and radiographic data for the patients will be obtained for characterization and classification of the fracture. After randomization, allocation of the patient into the study group and definition of the type of treatment to be performed, parameters related to the preoperative period will be acquired (Table 2).

**Table 2 Tab2:** Variables collected in the preoperative period

Level of fracture	
Neurological status (ASIA scale)	
Type of fracture (Magerl’s classification)	
Comorbidities	
Associated lesions	
Fracture of upper limbs	
Fracture of pelvis or lower limbs	
Charlson comorbidity index	
EUROQL-5	
Short-form SF-36	
HADS (Hospital Anxiety Depression Scale)	
Pain (VAS)	
AP Rx- vertebral alignment	
Lateral Rx- height of the fractured vertebral body, height of the vertebral body above and below the fractured vertebra, kyphosis of the injured vertebral segment, kyphosis of the fractured vertebra, sagittal index (Farcy index)	
CT- compression of the spinal canal, sagittal and coronal diameters of the spinal canal, lamina fracture	

Intra-operative parameters related to the surgical procedure will also be acquired (Table 3).

**Table 3 Tab3:** Variables collected in the intra-operative period, related to the surgical procedure

Type of approach (open/percutaneous)	
Operating time	
Intraoperative blood loss	
C-arm exposure	
Surgical drain	
Implants – mono or polyaxial screw/diameter/length/rods	
Intra-operative adverse events – (anesthesia, hemorrhage, dural lesion, neurological lesion)	
Intra-operative change of implants	

During the immediate postoperative period up to the moment of hospital discharge, data regarding the clinical evolution of the immediate postoperative period, use of analgesic medication, immediate postoperative complications, and postoperative imaging tests will be collected to evaluate the radiographic parameters (Table 4).

**Table 4 Tab4:** Variables collected in post-operative and hospital discharge parameter

Drainage – (48 h)	
VAS – 3 days postoperative	
Deambulation	
Complications – superficial infection, deep infection, neurological lesion, vascular lesion, hematoma	
Analgesics- drug, dosage, period of administration	
Antibiotics- drug, dosage, period of administration	
Number of the days from surgery till hospital discharge	
Adverse effects	
Reoperation	
AP Rx- vertebral alignment	

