### Secondary outcomes

The EUROQOL-5 and Short-form health survey (SF-36) will be used as generic quality of life questionnaires. The Roland Morris disability questionnaire will be used as a specific outcome for low back pain, and the capacity to work will be evaluated according to Dennis’s work scale. The HADS (Hospital Anxiety Depression Scale) will be evaluated preoperatively and during follow-up.

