### Secondary endpoints and safety profile

Considering the secondary outcomes (including minor and major adverse events [AE]), comparing the two groups (A versus B), and for comparing variables between groups A and B, when dealing with proportions, the chi-square test will be used, while for continuous variables the Student’s *t* test (if equal variances) will be used when dealing with averages or the Bonferroni e Benjamini-Hochberg test in the case of medians, in both cases, for independent samples. To minimize the interference of possible confounding variables (in both primary and secondary outcomes), all analyzes will be performed using necessary adjustments such as logistic regression, subgroup analyzes (age, sex, fracture type, duration of surgery, participant center, etc). A significance level of 5% shall be considered in all of the analyses described above.

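### Pre-operative ASIA status is collected but not named as a covariate for the functional secondary scores, which risks an avoidable loss of precision

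*Protocol article*

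**What the plan says.** **Eligibility.** Under Patient selection, "Neurological deficit is considered in the evaluation but not in the inclusion or exclusion criteria", except where posterior decompression is indicated. The same section says that "patients with neurological deficit that do not need a posterior decompression can be enrolled in the study". It also covers complete deficit: "In patients with total neurological déficit and no indication for canal decompression the treatment can be performed just by a posterior approach". The population can therefore run from neurologically intact to complete deficit.

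**Data.** Table 2 (Outcome measurements) lists "Neurological status (ASIA scale") among the pre-operative variables. SF-36, EUROQOL-5 and HADS are in the same table. Roland Morris and Dennis's work scale appear only in Table 5, at follow-up.

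**Outcomes.** Quality of life is measured with EUROQOL-5 and SF-36. On disability, the Secondary outcomes section states: "The Roland Morris disability questionnaire will be used as a specific outcome for low back pain". Work capacity is measured on Dennis's work scale.

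**Randomisation.** "The randomization process will be performed for each fracture type (A, B and C"). No other stratification factor is named.

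**Analysis.** Secondary endpoints and safety profile gives chi-square for proportions and Student's t for averages. It then promises adjustment of all analyses, primary and secondary, as needed. The example given is logistic regression, together with "subgroup analyzes (age, sex, fracture type, duration of surgery, participant center, etc"). Neurological status is named neither there nor in the similar list under Complications, adverse events, and additional surgery.

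**The concern.** Roland Morris, SF-36 and EQ-5D all depend in part on physical function. A cord or nerve deficit present before surgery is likely to predict these scores whichever approach is used. If the arms are compared by a plain t test, the spread between patients with and without deficit stays in the error term and the confidence interval is wider than it needs to be.

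The adjustment sentence does not settle this, for three reasons:

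- It fixes no covariate, so the choice could be made after the data are seen.
- The one model it names, logistic regression, does not suit continuous scores.
- It lists duration of surgery, which arises after randomisation, may be changed by the surgical approach, and is itself a secondary outcome in the Abstract. A baseline measure likely to predict function is left out.

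At stake is the precision of the functional and quality-of-life comparisons.

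**Working it through.** **Patients per arm.** The protocol states 58 per group. The pooled two-proportion formula with p1 = 0.50, p2 = 0.25, z = 1.96 and 0.84 reproduces it:

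[1.96·√(2·0.375·0.625) + 0.84·√(0.25 + 0.1875)]² / 0.25² = 57.6, so 58.

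(The unpooled formula as printed gives 2.8²·0.4375/0.0625 = 54.9, so 55. Nothing below depends on this.) With the stated 28% dropout, 58 × 0.72 = 41.8, or about 42 evaluable per arm. The secondary scores have no power statement of their own.

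**Assumed, because the document does not give them.** q is the share with deficit. g is the gap in mean score between patients with and without deficit, in within-stratum SDs. A true between-arm difference of 0.5 total SD is used for illustration.

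**Formulas.**

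- v = q(1 − q)g²
- Variance explained: R² = v/(1 + v)
- Ratio of adjusted to unadjusted SE: √(1 − R²)
- Equivalent patients per arm: n/(1 − R²)
- Power: Φ(0.5·√(n/2)/√(1 − R²) − 1.96)

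Unadjusted, n = 42: Φ(0.5·√21 − 1.96) = 63.0%.

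| q | g | R² | SE ratio | Equivalent n (from 42) | Power |
|---|---|---|---|---|---|
| 5% | 0.5 | 0.012 | 0.994 | 42.5 | 63.5% |
| 5% | 1 | 0.045 | 0.977 | 44.0 | 65.0% |
| 10% | 1 | 0.083 | 0.958 | 45.8 | 66.7% |
| 20% | 1 | 0.138 | 0.928 | 48.7 | 69.4% |
| 20% | 1.5 | 0.265 | 0.857 | 57.1 | 76.2% |
| 30% | 2 | 0.457 | 0.737 | 77.3 | 87.5% |

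The exact t distribution gives values about one point lower (62.0% unadjusted, 86.7% in the last row). With all 58 per arm, power is 76.8% unadjusted, and 78.7% to 95.5% over the rows from (5%, 1) to (30%, 2).

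**Is chance imbalance an additional harm?** Take q = 20% and g = 1.5, so v = 0.36. In within-stratum units, the unadjusted variance of the difference is (2/42)(1 + v) = 0.0476 + 0.0171. The variance due to imbalance in the share with deficit is g²·2q(1 − q)/42 = 2.25 × 0.00762 = 0.0171, which is exactly the second term. Imbalance is already in the unadjusted SE and must not be counted again. As an illustration, a 2-SD imbalance is 2 × 0.087 = 0.175. It shifts the difference by 0.175 × 1.5 = 0.26 within-stratum SD, or 0.26/√1.36 = 0.22 total SD. That is about one unadjusted standard error (√(2/42) = 0.218).

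**The case against.** A reader might infer that neurological status is shut out of the analysis. The text does not support that. The adjustment sentence covers all analyses and its list is open, and Patient selection says that deficit is considered in the evaluation.

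It can also be said that an article may leave the final covariate list to a fuller plan, and that singling out ASIA is a preference, since associated fractures and the Charlson index are in Table 2 too. This has some force: omission of a name alone would be a thin point. What stands is that the text does fix something, and fixes it badly: an unadjusted test for averages, a model unsuited to continuous scores, and a post-randomisation factor in the list.

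A second tempting reading is that the functional comparisons are biased. They are not: randomisation balances deficit in expectation, and the type I error of the t test is preserved.

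Three limits on the size stand in full:

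- The share with deficit and its effect are assumed. Patients with an indication for posterior canal decompression are excluded, so the share could be small.
- SF-36 and EQ-5D have pre-operative values that could take up part of the gain, and so could fracture type if deficit is related to it. For Roland Morris and the work scale, Table 2 lists no pre-operative value, although Patient selection says in general terms that baseline outcome scores are collected.
- The t-test figures do not carry over to an ordinal work scale.

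**Conclusion.** The point holds as an inexpensive improvement to secondary-outcome precision. The plan collects a pre-randomisation variable likely to predict function, names an unadjusted test for the scores concerned, and leaves the promised adjustment too open to secure the gain.

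Under 5–30% with deficit and a 1–2 SD gap, the SE falls by about 2–26%. If deficit is rare and its effect modest (5%, 0.5 SD), the gain is 0.6% of the SE. These figures assume that nothing else in the model explains the same variance and that the treatment difference is the same with and without deficit. The document cannot show where in the range the trial lies.

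**What to change.** In Secondary endpoints and safety profile, replace the plain t test for Roland Morris, SF-36 and EQ-5D with a linear model (ANCOVA). It should contain treatment arm and pre-operative ASIA deficit (yes/no) as a prespecified covariate, plus the pre-operative score for SF-36 and EQ-5D. State that between-arm comparisons are not adjusted for duration of surgery.

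For Dennis's work scale, ordinal regression with the same ASIA covariate may be used, stating that the estimate is a conditional odds ratio.

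The ASIA term costs one degree of freedom and a line or two of analysis wording. All the covariates are already in Table 2, so no new data are needed, and nothing in recruitment or randomisation changes.

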### Informed consent and patient safety

The patient will be asked to sign the informed consent form. Pre-operative baseline data will be collected for the outcome scores, patient demographic characteristics and classification and characterization of the injured vertebral segment. A patient who meets the inclusion criteria will be informed about the study. The therapeutic options as well as their benefits and risks will be explained, and the patient will be free to participate in the study. If the patient is willing to participate in the study, written informed consent will be obtained.

The patients will be notified that they are free to withdraw from the study at any time. Adverse effects or complications will be treated and followed up until the issue is stable or resolved. The study was submitted to and approved by an institutional review board (IRB) trial registration, ClinicalTrials.gov Protocol Registration and Results System (PRS): NCT03316703, Approval Number: 1.933.631, study start in june 1, 2017.

### Randomization

Patients who meet the inclusion criteria and have provided informed consent will have their fractures classified according to the system proposed by Magerl et al. The randomization process will be performed for each fracture type (A, B and C). The patients will be randomly allocated into the following two groups: A- conventional open surgery and B- minimally invasive percutaneous surgery. The randomization will be performed via a centralized system. The research team will contact the central randomization system informing the type of fracture (A, B or C). The type of treatment will then be assigned by this system, with the patient being subsequently allocated to the appropriate group. We will use envelopes for each fracture type, following the CONSORT (Consolidated Standards of Reporting Trials) guidelines. The randomization will be performed using numbers generated by a specific software [MedCalc Statistical Software version 18.11.3] and will obey the 1:1 ratio for each group [MedCalc Software bvba, Ostend, Belgium; https://www.medcalc.org; 2019].”general anesthesia. Stability of the spine will be achieved by bilateral short-segment pedicle instrumentation. Pedicle screws will be inserted into the vertebral body one level above and below the fractured vertebra. The fractured vertebra will also be included in the fixation. In the fractured vertebra, a short pedicle screw will be inserted uni- or bilaterally according to the degree of pedicle involvement.

The spine fixation system is composed of a 6.5-mm-diameter polyaxial pedicle screw attached to 5.5 mm rods. The vertebral fixation system will be applied through the conventional open approach in group A (open approach) and percutaneously without open exposition of the injured vertebral segment in group B (minimally invasive percutaneous surgery). Posterior fusion using bone grafts or bone substitutes will not be performed in either group. External immobilization will not be used after surgery, and the patients will be allowed to walk according to their general clinical picture and pain.

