### Primary outcome measure

The pain intensity after the surgical procedure will be evaluated using the VAS. The pain is related by the patient on a 100 mm horizontal visual analog scale. The two ends of the scale are 0 mm (no pain) and 100 mm (the most terrible pain that I can imagine). The patient will be asked to mark the scale based on their average pain during the evaluation period. The pain intensity will be evaluated before and after the surgical procedure. After surgery, pain will be evaluated on the first three postoperative days and at 1, 2, 3, 6, 12 and 24 months after the surgical procedure. Pain will also be evaluated according to Dennis’s scale at the 1, 2, 3, 6, 12 and 24 month follow-up visits.

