### Statistical considerations

#### Sample size

Considering an expected reduction of two points in the visual analog pain scale (VAS) in 50% of the patients in group B compared to 25% those in group A after surgery with a significance level of 5% and a study power of 80%, and using the Z statistic, where p_1_ (0.5) and p_2_ (0.25) are previously defined, a minimum sample size of 58 patients was obtained, for each of the groups, according to the following formula:
$$ \mathrm{n}={\left( Z\alpha / 2+{Z}_{\beta}\right)}^2\ast \left({p}_1\left( 1-{p}_1\right)+{p}_2\left( 1-{p}_2\right)\right)/{\left({p}_1-{p}_2\right)}^2 $$

Where, Zα/2 is the critical value of the Normal distribution at α/2, i.e., 0.05 and critical value =1.96; Z_β_ is the critical value of the Normal distribution at β, i.e., 0.2 and critical value = 0.84; p_1_ and p_2_ are the previously defined sample proportions of the two groups.

Assuming an alpha of 0.5, a sample size of 58 patients per group was calculated to yield a power of 80% and detect a difference of one point between intervention groups in the 10-point VAS score. Standard differences were estimated to be 1.6 according to previous work (1) and drop-out rates were anticipated to be 28%”.

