### Statistical analysis

In the multicenter, randomized clinical trial, comparisons between proportions for the categorical variables will be carried out with the Chi-square test. For verification of differences between measures of central tendency, Student’s t tests for paired samples will be used in the intragroup analysis and for independent samples will be used for the intergroup analysis. In case of comparisons between medians, the Kruskal-Wallis test or another hypothesis test for non-parametric continuous variables will be used.

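### The plan does not fix one adjusted primary model: the named tests omit fracture type and baseline VAS, and the later adjustment clause is open-ended and includes duration of surgery

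*Protocol article*

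**What the plan says.** **Design.** The Randomization section of the protocol article states: "The randomization process will be performed for each fracture type (A, B and C"). Each list "will obey the 1:1 ratio for each group". No block size or other device to force balance within a fracture type is described.

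**Baseline pain.** Under Primary outcome measure: "The pain intensity will be evaluated before and after the surgical procedure". Preoperative VAS is also listed in Table 2. Patient selection and Informed consent place baseline collection next to consent. Outcome measurements says the Table 2 variables are acquired after randomisation and allocation.

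**Named methods.** Statistical analysis gives the chi-square test for proportions and, for means, Student's t-test: paired within groups, and "for independent samples will be used for the intergroup analysis". Primary outcome (analysis) gives the relative risk with its 95% confidence interval and derived measures, by intention to treat. It assigns univariate then multivariate logistic regression to associations among the other variables. No stratum or baseline covariate is attached to the treatment comparison.

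**Adjustment clause.** Secondary endpoints and safety profile says that, to limit confounding in primary as well as secondary outcomes, all analyses will use whatever adjustment is needed. It gives logistic regression and subgroup analyses as examples, with an open-ended list: age, sex, fracture type, duration of surgery and centre. Baseline VAS is not on the list. The section on complications and adverse events gives nearly the same list as subgroup analyses and describes them as post hoc.

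**The concern.** A stratification factor and a baseline measurement of the primary outcome are the two covariates one would expect in the primary model. Here the named tests carry neither. The only clause that might bring them in does not say which model gives the main result.

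Three things are at stake:

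- **Which estimate is primary.** An unadjusted relative risk, an unadjusted t-test and several adjusted analyses could each be presented as planned.
- **Validity of an adjusted estimate.** Duration of surgery is measured after randomisation, is likely to be affected by the approach, and is itself a secondary outcome in the Abstract. Adjusting for it could remove part of the treatment effect or bias it.
- **Precision.** Baseline pain is already collected, but no between-arm model is said to use it.

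**Working it through.** **Step 1. Reproduce the plan's sample size.** Inputs from Sample size: two-sided alpha 0.05, power 0.80, and a two-point VAS reduction expected "in 50% of the patients in group B compared to 25% those in group A after surgery". The stated result: "a minimum sample size of 58 patients was obtained, for each of the groups".

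- Printed (unpooled) formula: (1.96 + 0.84)² × (0.25 + 0.1875) / 0.25² = 7.84 × 0.4375 / 0.0625 = 54.88, so 55.
- Pooled-variance version: 57.7, so 58. This matches the stated figure.
- Second justification, to "detect a difference of one point between intervention groups in the 10-point VAS score" with SD 1.6 and 28% drop-out: 41 per arm evaluable, and 41 / 0.72 = 56.9, so 57. This is close to 58 if the printed alpha of 0.5 is read as 0.05.
- Evaluable patients from 58: 58 × 0.72 = 41.8 per arm.

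Neither calculation takes credit for covariate adjustment.

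**Step 2. Gain from baseline VAS (mean VAS).** Adjustment reduces the SD to 1.6 × √(1 − ρ²), where ρ is the correlation of baseline with follow-up VAS. The protocol gives no ρ, so a range is assumed, and 1.6 is taken as the unadjusted SD. With 41 per arm, power = Φ(1/SE − 1.96).

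Unadjusted: SE = 1.6 × √(2/41) = 0.353; 1/0.353 = 2.83; Φ(0.87) = 80.8%.

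| Assumed ρ | Adjusted SD | Interval width relative to unadjusted | Power |
|---|---|---|---|
| 0.1 | 1.592 | 0.995 | 81.2% |
| 0.2 | 1.568 | 0.980 | 82.3% |
| 0.3 | 1.526 | 0.954 | 84.3% |
| 0.5 | 1.386 | 0.866 | 90.4% |
| 0.7 | 1.143 | 0.714 | 97.7% |

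The t-distribution with 42 per arm gives the same figures to within 0.1 percentage point.

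**Step 3. Cost of ignoring fracture type, if arms are balanced within each type.** Let fracture type explain a share R² of the VAS variance (assumed). The true variance of the difference is then (1 − R²) times what the unadjusted test estimates. With f = 1/√(1 − R²):

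- the interval is too wide by the factor f
- type I error = 2 × (1 − Φ(1.96 f))
- power is Φ((2.83 − 1.96) f) unadjusted and Φ(2.83 f − 1.96) adjusted

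| Assumed R² | Interval too wide by | Type I error | Power unadjusted | Power adjusted |
|---|---|---|---|---|
| 0.02 | 1.0% | 4.8% | 81.0% | 81.6% |
| 0.05 | 2.6% | 4.4% | 81.4% | 82.7% |
| 0.10 | 5.4% | 3.9% | 82.0% | 84.7% |
| 0.20 | 11.8% | 2.8% | 83.5% | 88.6% |

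**Step 4. Does the adjustment clause settle the model?** It reaches the primary outcome and lists fracture type, so it points towards adjustment. It does not fix a model, for four reasons:

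1. Its list is open, and it does not separate covariates from subgroups.
2. The complications section calls nearly the same list of subgroup analyses post hoc. A post-hoc subgroup analysis does not replace a stratified primary comparison.
3. The list includes duration of surgery.
4. Logistic regression, the only model named, does not apply to mean VAS and yields odds ratios rather than the relative risk the plan promises.

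**The case against.** **Fracture type is covered.** A reader who stops at the named tests might infer that the primary analysis simply ignores both variables. The documents do not support that: the adjustment clause covers the primary outcome and names fracture type. This part of the objection stands. What remains is that the clause leaves the model open and mixes in an unsuitable variable.

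**The detail belongs in an analysis plan.** A condensed article may leave exact covariates to a document not shown here, and an open list could include baseline VAS. That is fair for the missing name taken alone. It does not excuse what the article does state: one section's unadjusted tests beside another's promise of adjustment, the post-hoc label, and duration of surgery on the list.

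**The error-rate figures need balance.** Separate lists at 1:1 without stated blocking do not force balance within fracture types. Under simple randomisation in each stratum, the unadjusted test stays at about its nominal level. This stands, so the Step 3 figures are conditional.

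**Baseline may already be in the endpoint.** If the two-point reduction is counted from the preoperative score, baseline VAS enters the responder definition, though not as a covariate. The reference point is not stated.

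**Paired tests.** A reader might infer that the within-group t-tests are meant to show a treatment effect. The protocol assigns them only to the intragroup analysis and does not say that.

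**Conclusion.** The point holds in a limited form. The protocol stratifies by fracture type and measures VAS before surgery, but does not commit to one primary model using both. As written, the main estimate may be unadjusted, or adjusted for a variable that the operation itself influences.

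The two omissions differ in kind. Leaving out baseline VAS gives a valid but less precise interval: about 3 to 17 percentage points of power for correlations of 0.3 to 0.7, and under 2 points at 0.2 or less. Leaving out fracture type makes the interval too wide and the test conservative only if strata are balanced, by the 1% to 12% shown, costing about 0.6 to 5 points of power. Both ranges rest on an assumed ρ or R² and apply to mean VAS. No figure is available for the relative risk on a responder endpoint.

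It would be wrong to infer an inflated false-positive rate from these omissions, since any error is on the conservative side. The risk of bias comes from adjusting for duration of surgery. The change should be made, but the trial's validity does not hang on the two omitted covariates.

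**What to change.** - State one primary model. For VAS as a continuous outcome, use a linear model with arm, baseline VAS and fracture type (A, B, C). If the primary endpoint is the responder proportion, use Mantel-Haenszel relative risk and risk difference stratified by fracture type, and state the score from which the two-point reduction is counted.
- Label the unadjusted t-test, chi-square test and relative risk as supportive.
- Separate covariate adjustment from subgroup analysis, close the covariate list, and reconcile it with the post-hoc label in the complications section.
- Remove duration of surgery from the adjustment set. It can stay as a secondary outcome.
- Reconcile Patient selection and Informed consent with Outcome measurements on when Table 2 data are taken, and confirm that baseline VAS is recorded before allocation is known. A self-reported score given after allocation is a weaker covariate.

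The cost is wording, plus a check at the five centres on when baseline VAS is recorded. No new variable and no extra patients are needed. The text should be settled before any outcome data are compared by arm.
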